### Sample size

The incidence of falls in this population is uncertain, but based on previous studies is estimated to be about 0.27 [8, 12]. If the expected result is 0.27, we want 95% confidence, within a 1% absolute margin of error that the true incidence rate frequency lies between 0 and 1.27 [31]. Therefore a minimum sample size of 78 has been estimated to be required for Phase 1 of the study. As the study population has both physical and social disability and the observation period extends for six months, a drop out of approximately 15%, will be allowed for, which is higher than the 5% drop-out in a previous observational falls cohort study of older people [32]. Therefore the aim is to recruit 90 participants for Phase 1.

A purposeful sample [33] will be utilised for Phase 2. The aim is to purposefully select participants who have experienced a fall(s) in Phase 1 with different characteristics and/or consequences of the fall, in order to achieve a close representation of the experience older adults with ID have when accessing evidence based fall prevention recommendations. The aim is to be able to provide a holistic perspective about falls among people with ID and participants will be purposefully selected to represent those recruited. This sample will be guided by the participants who fall in Phase 1. Where possible, purposeful selection will include participants of different gender, age, diagnosis, level of independence and differing levels of communication (including verbal and non-verbal participants). Participants with different living arrangements (living with family or independently with or without support) and those who report varying circumstances surrounding their falls will also be considered when selecting the sample. Interviews will be continued until it is considered that saturation of themes has occurred [34] however it is understood that amongst this ‘hard-to-reach’ population this may not be entirely achievable.

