### Outcome measures

The primary outcome of phase 1 will be the number of falls experienced by participants during the six month trial period. A fall is defined as ‘an event which results in a person coming to rest inadvertently on the ground or floor or other lower level’ [35]. Fall events will be collected prospectively with daily recordings of any fall occurrences for six months [14]. The participants will be provided with a monthly calendar for six months on which they, or their caregiver, will mark a cross on the day(s) if a fall occurs and draw a smiley face on day(s) where a fall is not experienced. The diary has a prominent phone number on it and participants are encouraged to contact the researcher at any time. It is envisaged that family and caregivers (paid and unpaid) will be providing substantial support and sometimes will be entirely relied upon to collect the falls data. If families or caregivers find that this method of data collection is not accurate, such as if daily recordings are not sustainable, other strategies may be discussed and put in place as appropriate. These strategies may include but not limited to, the researcher making contact more frequently, making contact with more than one caregiver or leaving a falls record form with questions from the post-fall telephone interview. Other strategies used are initiating contact with participants and also informing others who support the participant to be aware of their participation, to ensure that all falls are recorded. At the end of the month, the participants are asked to send the calendar back to the researcher. The researcher will follow up with a phone call at the end of every month to enquire if a fall has occurred or if they have trouble filling up the diary. When a fall occurs, participants are encouraged to contact the researcher. Caregivers are also encouraged to call when a fall is witnessed or when an unwitnessed fall is suspected. The details of the circumstances of the fall and any falls related injuries will be collected through a telephone call or face to face interview. This procedure follows recommended guidelines for conducting falls research [14]. Data about the fall such as, where and when the fall occurred, what happened at the time of the fall and if the fall is a result from a seizure will be collected. The number, type and location of any resulting injuries and any medical or first aid attention received will also be recorded. A fall will be classified as injurious if it results in bruising, laceration, dislocation, fracture or complaint of an onset of persistent pain as a result of the fall, which is concordant with previous research conducted in this area [32].

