### Statistical analysis

#### Quantitative data analysis

Data will be analysed using the SPSS 23.0 software package (SPSS Inc., Chicago, IL, USA) and STATA 14.0 (StataCorp. 2015. Stata Statistical Software: Release 14. College Station, TX: StataCorp LP). Descriptive statistics will be used to describe the clinical and demographic characteristics of the participants. Falls analyses will follow recommended statistical guidelines for analysing falls data [32, 45].

The primary outcome measure (rate of falls) will be expressed as an incidence rate per person year. The number of participants who experienced a fall will be expressed as a percentage of people falling in the cohort. The rate of injurious falls will be expressed as the incident rate per person year. Generalised linear mixed modelling will be conducted to examine participant and their clinical characteristics predictive of falls, injurious falls and the risk of falling in the six months after commencement of the falls diary.

The modelling strategies will start with unadjusted univariate analysis, followed by multivariate analysis, adjusting for age, severity of ID, presence or absence of epilepsy, level of assistance required with activities of daily living, level of mobility and a history of falls in the six months prior to enrolment in the study. These variables have been shown to be predictive of falls in either older people or people with ID.

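### The target of 90 covers about 13% drop-out rather than 15%, and a crude percentage of fallers would run slightly low if its denominator is everyone enrolled

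*Protocol article*

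**What the plan says.** In the protocol article, Sample size, the plan states that "a minimum sample size of 78 has been estimated to be required for Phase 1 of the study". It adds that "a drop out of approximately 15%, will be allowed for", and describes this as "higher than the 5% drop-out in a previous observational falls cohort study of older people". It concludes: "Therefore the aim is to recruit 90 participants for Phase 1". Setting and recruitment says that enrolment continues until 90 is reached, so 90 is the working stopping figure.

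On the analysis side, Quantitative data analysis expresses the primary outcome as falls per person-year. For the proportion who fall it says: "The number of participants who experienced a fall will be expressed as a percentage of people falling in the cohort". The Method part of the Abstract describes the cohort as having n = 90. Neither place says how someone who leaves before any fall is to be classified.

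**The concern.** There are two separate matters, and both turn on expected drop-out.

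1. **The recruitment target.** To keep 78 people after losing 15%, one divides 78 by 0.85. Multiplying by 1.15 gives a smaller number, and the resulting target then misses the protocol's own minimum at its own stated loss.

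2. **The proportion who fall.** A crude percentage over everyone enrolled keeps a person lost in month 2 in the denominator for all six months, although any later fall cannot reach the numerator. The figure would then run low. It matters because the Background names the proportion who fall as a recommended measure and cites earlier studies reporting 25 to 40.1%, so readers will set the new figure beside those.

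**Working it through.** **Inputs.** Minimum 78, drop-out of approximately 15% and target 90 come from Sample size. Six months of daily diary recording comes from Outcome measures. Cohort n = 90 comes from the Abstract. The 78 is taken as stated; whether it follows from its own inputs is a different question.

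**Recruitment target**

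- Reproducing the plan's figure: 78 × (1 + 0.15) = 89.7, rounded up to 90. It matches exactly.
- Inflation that keeps 78 after 15% loss: 78 / (1 − 0.15) = 91.8, rounded up to 92. Check: 92 × 0.85 = 78.2.
- Completers from 90 at 15% loss: 90 × 0.85 = 76.5, against 78.
- Loss that 90 can absorb: 1 − 78/90 = 13.3%.

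**What the shortfall costs**

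- For an illustrative proportion of 0.27, the 95% half-width is 1.96 × √(0.27 × 0.73 / n): 9.85 points at n = 78 and 9.98 points at n = 76.
- For the rate per person-year, follow-up time is what counts. If 15% leave evenly over the six months, each contributes half the period on average: 90 × (0.85 + 0.15 × 0.5) = 83.25 six-month equivalents, above 78. Only if every drop-out contributed nothing would the total be 76.5.

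**Proportion who fall, if the denominator is all enrolled**

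Assumptions that are not in the documents: a true six-month proportion p, constant risk of a first fall, 15% lost uniformly over the six months, and loss unrelated to fall risk. Sample size gives 0.27 without a unit, so reading it as a six-month proportion of 27% is also an assumption. The 40% is a second illustration.

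- Hazard over six months: λ = −ln(1 − p).
- Chance that a person who drops out falls before leaving: f = 1 − p/λ.
- Crude percentage: 0.85 × p + 0.15 × f.

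| True p | λ | f | Crude, even loss | Crude, all lost at the start (0.85 × p) |
|---|---|---|---|---|
| 27% | 0.315 | 0.142 | 22.95% + 2.13% = 25.1% | 23.0% |
| 40% | 0.511 | 0.217 | 34.0% + 3.25% = 37.3% | 34.0% |

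With even loss the deficit is about 1.9 and 2.7 points, roughly 7% in relative terms. The all-at-start column is the extreme case.

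**The case against.** The case against giving this weight is strong on several counts.

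- The allowance is only approximate. A loss of 13.3% could pass as roughly 15%, the gap is one or two people, and the plan already regards its allowance as cautious against the earlier 5%. This stands, and it is why the target need not change.
- A count of completers is not the right yardstick for a rate per person-year, because partial follow-up contributes. This also stands.
- The article does not say that people lost before falling are counted as non-fallers. A completers-only denominator would not produce this bias when loss is unrelated to risk. Such detail may sit in a fuller plan, and the article says that falls analyses follow published guidelines. This stands as a limit: the bias is conditional on the all-enrolled denominator. That denominator is nevertheless the natural reading, since the Abstract puts the cohort at 90 and the percentage is stated for the cohort.

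A reader might infer three stronger things that the text does not support. One is that drop-out is systematically mishandled; in fact there is one small arithmetic slip and one unspecified denominator. Another is that the bias equals the attrition; under even loss it is about 7% relative, not 15%. The third comes from reading the percentage sentence literally, with fallers as their own base. That would always give 100%, so it is awkward wording; the Background shows that the proportion of people who fall is meant.

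**Conclusion.** The point holds in a limited form.

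The arithmetic slip is certain from the plan's own numbers: 90 provides for about 13% loss, not 15%. Its effect is negligible, at 0.13 points on an illustrative half-width of about 10, and with little or no effect on the precision of the primary rate.

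The understatement of the proportion who fall is conditional. It needs an all-enrolled denominator, and its size rests on 15% loss that is even over time and unrelated to risk, with constant hazard. On those terms 27% becomes about 25% and 40% about 37%. That is small beside a sampling half-width of about 10 points, and it touches a secondary descriptive measure, not the primary rate. It is worth acting on because the remedy uses data that the study already collects.

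**What to change.** 1. In Sample size, restate the drop-out allowance as about 13% and leave the target at 90. The cost is one reworded sentence.

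2. In Quantitative data analysis, report the six-month proportion who fall as a Kaplan-Meier cumulative incidence of first fall, censoring at last diary contact. Give beside it the raw number of fallers over the number enrolled. No new data are needed: the plan says "Fall events will be collected prospectively with daily recordings of any fall occurrences for six months", and the monthly calendar returns and calls give the date of last contact.

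The cost is a little extra analysis and the assumption that people who leave have the same later fall risk as those who stay. That assumption should be stated with the result, since the estimate does not protect against loss that depends on fall risk.

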### Outcome measures

The primary outcome of phase 1 will be the number of falls experienced by participants during the six month trial period. A fall is defined as ‘an event which results in a person coming to rest inadvertently on the ground or floor or other lower level’ [35]. Fall events will be collected prospectively with daily recordings of any fall occurrences for six months [14]. The participants will be provided with a monthly calendar for six months on which they, or their caregiver, will mark a cross on the day(s) if a fall occurs and draw a smiley face on day(s) where a fall is not experienced. The diary has a prominent phone number on it and participants are encouraged to contact the researcher at any time. It is envisaged that family and caregivers (paid and unpaid) will be providing substantial support and sometimes will be entirely relied upon to collect the falls data. If families or caregivers find that this method of data collection is not accurate, such as if daily recordings are not sustainable, other strategies may be discussed and put in place as appropriate. These strategies may include but not limited to, the researcher making contact more frequently, making contact with more than one caregiver or leaving a falls record form with questions from the post-fall telephone interview. Other strategies used are initiating contact with participants and also informing others who support the participant to be aware of their participation, to ensure that all falls are recorded. At the end of the month, the participants are asked to send the calendar back to the researcher. The researcher will follow up with a phone call at the end of every month to enquire if a fall has occurred or if they have trouble filling up the diary. When a fall occurs, participants are encouraged to contact the researcher. Caregivers are also encouraged to call when a fall is witnessed or when an unwitnessed fall is suspected. The details of the circumstances of the fall and any falls related injuries will be collected through a telephone call or face to face interview. This procedure follows recommended guidelines for conducting falls research [14]. Data about the fall such as, where and when the fall occurred, what happened at the time of the fall and if the fall is a result from a seizure will be collected. The number, type and location of any resulting injuries and any medical or first aid attention received will also be recorded. A fall will be classified as injurious if it results in bruising, laceration, dislocation, fracture or complaint of an onset of persistent pain as a result of the fall, which is concordant with previous research conducted in this area [32].

Baseline demographic data including age and other medical history such as diagnosis including number of comorbidities, any history of fracture, stroke or other condition affecting falls risk, number and type of medications, history of visual impairment and falls history, which have been previously identified as being risk factors for falls [9] will be collected. Other measures known to be associated with falls in people with ID [5, 13] that are collected at baseline will be body mass index, indoor and outdoor mobility, use and type of walking aid and classification of Intelligence Quotient score when known. Other supporting information about the participants that will be collected include education and employment history and level of care support. Functional measures of mobility using Timed-up and Go [36], balance using Four step-square test [37], and the Four-test balance Scale [38]. Five times Sit to Stand [39] will be used to measure lower limb strength. These physical outcome measures will be first carried out using standardised procedures [36–39]. Where required, the procedure will be modified appropriately and documented according to the participant’s communication styles and understanding. Strategies used to modify the instructions include the methods described in Salb et al.[40] which have demonstrated that the reliability of these tests used with people with ID is still maintained. Participants’ ability to perform activities of daily living will be measured using The Katz Index of Independence in Activities of Daily Living [41]. The Personal Well-being Index for people with ID [42] will be used to collect the participant’s perspective on their perceived health related quality of life (HRQoL). Where participants are unable to rate their HRQoL, the EQ-5D-5 L [43] will be used to ask caregivers to act as a proxy to rate the participant’s HRQoL as they perceive it.

Qualitative data gathered during Phase 2 of the study will explore the participants’ experience when accessing falls prevention services after experiencing a fall. These data will be collected using structured face-to-face interviews, which will be conducted and recorded by the researcher (PH), who is a therapist who is experienced in working with people with ID. Questions will be modified as appropriate using various strategies such as having a familiar family member and /or caregiver present to interpret the questions in the context in which the participant can understand. Participants who have limited verbal communication will be included in Phase 2. Where appropriate, alternative forms of communication (key word signs, augmentative and alternative communication devices, natural gestures) will be used to facilitate the interview. The researcher will provide additional support to the participant such as allowing time for them to express themselves, exploring the environment where the fall took place and where suitable drawing their attention to the part of their body where an injury was sustained.

Caregivers who were supporting the participant at the time of the fall or who provided support relating to treatment or intervention following the fall will be asked to participate in a separate interview, which will also be conducted by the researcher (PH). The participant (person with ID or a caregiver) will be asked to describe the events that took place after the fall with specific attention to any medical or healthcare services that they received. When required, the interviewer will prompt using a code, which has been designed around the recommended evidence based service pathway for falls prevention which is outlined in the WA falls model of care [44]. The interviewer will specifically ask the participant if they were seen by a medical provider after their fall, such as a medical hospital outpatient clinic or their family doctor for falls risk assessment, and if they were provided with any follow up referrals to an intervention such as physiotherapy for strength and balance exercises or an optometrist for a vision check. Open questions will be used to explore the experiences of the participants in further scope and depth. Participants will be asked if they sought and received the intervention or a plan was in place for them to undertake the intervention at a later date Depending on what the participants share, they will be asked if they encountered any barriers when seeking to undertake the intervention that was recommended.

### Statistical analysis

#### Quantitative data analysis

Data will be analysed using the SPSS 23.0 software package (SPSS Inc., Chicago, IL, USA) and STATA 14.0 (StataCorp. 2015. Stata Statistical Software: Release 14. College Station, TX: StataCorp LP). Descriptive statistics will be used to describe the clinical and demographic characteristics of the participants. Falls analyses will follow recommended statistical guidelines for analysing falls data [32, 45].

The primary outcome measure (rate of falls) will be expressed as an incidence rate per person year. The number of participants who experienced a fall will be expressed as a percentage of people falling in the cohort. The rate of injurious falls will be expressed as the incident rate per person year. Generalised linear mixed modelling will be conducted to examine participant and their clinical characteristics predictive of falls, injurious falls and the risk of falling in the six months after commencement of the falls diary.

The modelling strategies will start with unadjusted univariate analysis, followed by multivariate analysis, adjusting for age, severity of ID, presence or absence of epilepsy, level of assistance required with activities of daily living, level of mobility and a history of falls in the six months prior to enrolment in the study. These variables have been shown to be predictive of falls in either older people or people with ID.

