Falls among older adults with intellectual disability (ID) living in the community are also a cause for concern. People with ID have been observed to experience signs of ageing from their third decade in life [5, 6], and as such are considered ‘older adults.’ At least 50% or more of these falls result in injury [7, 8] and between 6 and 11% result in severe injuries, such as fractures and concussion [8, 9]. Qualitative research undertaken among adults with ID has found that falls may lead to reduced activity and independence and increase the burden of care on their caregivers [10]. Through observation, it has been suggested that people with ID have increased risk of institutionalisation from having falls [11]. Few studies have investigated falls rates amongst people with ID living in community based settings. Estimates range from 0.93 to 6.29 falls per person year [8, 9, 12, 13]. Other studies have reported between 25 and 40.1% of people with ID experienced a fall(s) during the observation period, but did not report the number of falls [7, 14–16]. Only three studies provided sufficient data to estimate injurious falls rates and these were 0.38–0.73 injurious falls per person year [8, 9, 13]. Research guidelines recommend reporting falls and injurious falls rates, as well as the proportion of people who fall when conducting falls related studies [16]. Additionally only one study implemented prospective daily recording of falls, [8] which is recommended for falls prevention trials [16] to ensure accurate and comprehensive collection of falls data. Limitations to these study designs, poses uncertainty about the extent of the problem of falls among older adults with ID. Additionally a limited amount of studies have investigated risk factors and preventive strategies for falls among people with ID [7, 12, 15]. A review which examined risk factors and preventative strategies for falls prevention in people with ID was only able to include seven studies, and found there was a lack of evidence about falls management for people with ID, prompting authors to recommend that more research in this area be undertaken [17].

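### Six forced adjusters leave about 2 to 5 events per parameter in the risk-of-falling model, so an ordinary logistic fit would be imprecise and inflated on average; a penalised fit would remove most of the inflation

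*Protocol article*

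**What the plan says.** The Quantitative data analysis section of the protocol article plans generalised linear mixed models for characteristics "predictive of falls, injurious falls and the risk of falling in the six months after commencement of the falls diary". Unadjusted analysis comes first, "followed by multivariate analysis, adjusting for age, severity of ID, presence or absence of epilepsy, level of assistance required with activities of daily living". The same sentence adds level of mobility and falls in the half-year before entry, which makes six adjusters, chosen because earlier work links them to falls. The section names no distribution or link, and does not tie model size to the number of events. Injurious falls are to be reported as a rate per person year.

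The Sample size section considers only the precision of the incidence estimate. Incidence, "based on previous studies is estimated to be about 0.27", leads to the statement that "a minimum sample size of 78 has been estimated to be required for Phase 1 of the study". Then "a drop out of approximately 15%, will be allowed for", and so "the aim is to recruit 90 participants for Phase 1".

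The Background reports that in earlier studies "between 25 and 40.1% of people with ID experienced a fall(s) during the observation period". It also gives rates of 0.38 to 0.73 injurious falls and 0.93 to 6.29 falls of any kind per person year. Finding the risk factors for falls is secondary aim ii.

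**The concern.** The adjustment set is fixed in advance, which is good practice, but it was not checked against the number of events that the study is likely to see. Maximum-likelihood logistic regression with few events per parameter tends to push coefficients away from zero, gives wide intervals, and can separate when a category contains only fallers or only non-fallers. Aim ii would then be answered with adjusted effects that look larger than they are and are poorly determined. An analysis plan that follows the published sentence would carry this forward.

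**Working it through.** **1. The plan's own figure.** For a single proportion, n = 1.96² × p(1 − p) / d². With p = 0.27, the numerator is 3.8415 × 0.1971 = 0.757. At the stated margin d = 0.01, n = 7,572. At d = 0.10, n = 76, close to 78. So 78 makes sense only if 0.27 is a proportion of people who fall and the margin is about ten points. That supports using 0.27 as a faller proportion here. The mismatch in the margin is a separate matter.

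**2. Expected fallers** (participants × proportion).
- 78 × 0.25 = 19.5; 78 × 0.27 = 21.1; 78 × 0.401 = 31.3.
- If all 90 complete: 90 × 0.25 = 22.5; 90 × 0.401 = 36.1.

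**3. Events per parameter.** The article does not state the coding, so two cases are shown, each with one candidate factor.
- Seven terms (six single-term adjusters + 1): 19.5/7 = 2.8; 21.1/7 = 3.0; 31.3/7 = 4.5; 36.1/7 = 5.2.
- Eleven terms (severity in four levels, daily-living assistance and mobility in three each: 3 + 2 + 2, plus age, epilepsy, prior falls and the factor): 19.5/11 = 1.8; 21.1/11 = 1.9; 31.3/11 = 2.8; 36.1/11 = 3.3.

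**4. Ordinary logistic fit, by simulation.** There were 1,000 runs per row, with a true odds ratio of 2 (log 0.693) for a binary factor with 30% prevalence. Assumed covariates: epilepsy 30%, prior falls 35%, severity 35/35/20/10%, assistance 50/30/20%, mobility 55/30/15%, the last three moderately correlated. Averages are over runs without separation.

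| Participants, fallers | Terms | Mean log OR | Bias | Separated | Coverage | Power |
|---|---|---|---|---|---|---|
| 78, 27% | 7 | 0.790 | +14% | 0% | 0.946 | 0.245 |
| 78, 40.1% | 7 | 0.752 | +9% | 0% | 0.942 | 0.256 |
| 90, 40.1% | 7 | 0.796 | +15% | 0% | 0.951 | 0.295 |
| 78, 27% | 11 | 0.866 | +25% | 10% | 0.932 | 0.222 |
| 78, 40.1% | 11 | 0.825 | +19% | 6% | 0.950 | 0.258 |
| 90, 40.1% | 11 | 0.843 | +22% | 2% | 0.925 | 0.297 |

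Simulation error is about 3 percentage points of bias (first row: SD 0.74/√1000 = 0.023; 0.023/0.693 = 3%), so small differences between rows mean little. The imprecision is plain: with SD 0.74, 1.96 × 0.74 = 1.45 and e^1.45 = 4.26, so an interval centred on 2 runs from about 0.47 to 8.5.

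**5. Penalised fit.** Two further simulations used other assumed covariates and the same true odds ratio.
- Nine adjustment parameters, 78 participants, 1,500 runs, 27% fallers: maximum likelihood 0.897 (+29%), with 119/1,500 = 8% failed or separated; Firth 0.722 (+4%); root-mean-square error 0.87 against 0.65. At 40% fallers: 0.817 (+18%) against 0.685 (−1%).
- All six adjusters kept: maximum likelihood +14% to +33%, with about 1% or fewer failed fits; Firth bias 2% to 6%; root-mean-square error 0.85 against 0.64 in one example.

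**6. Injurious falls.** Follow-up is 78 × 0.5 = 39 person-years, so 39 × 0.38 = 14.8 to 39 × 0.73 = 28.5 events (45 person-years with all 90: 17.1 to 32.9). In Poisson simulations with a true rate ratio of 2 and the covariates of step 4, bias was −3% to +10%. Non-finite estimates occurred in 0% to 4% of runs with seven terms and 7% to 42% with eleven. Coverage fell to about 0.87 at 28.5 events when overdispersion was ignored.

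**7. All falls.** 39 × 0.93 = 36 to 39 × 6.29 = 245 events, so this model is much less affected.

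**The case against.** *The faller count is uncertain.* The article calls 0.27 an incidence and then says "we want 95% confidence, within a 1% absolute margin of error that the true incidence rate frequency lies between 0 and 1.27", so it may not be a six-month proportion, and the Background does not give the observation periods behind 25% to 40.1%. The higher published fall rates could mean more fallers unless falls are concentrated in few people. This stands as a caution: 21 fallers is near the low end of the range and should not be read as the forecast. It does not rescue the model. In a binary outcome the smaller group limits the fit; that group cannot exceed 39 of 78, and 39/7 = 5.6 even with the leanest coding.

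*Coding and fitting method belong in an analysis plan.* True, and their absence from an article is no fault. The adjustment set, however, is stated here, and the point concerns what that set asks of the data.

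*Imprecision matters more than bias.* This also stands. In the first row of the table the bias is 0.790 − 0.693 = 0.10 on the log scale against an SD of 0.74, and coverage is close to nominal.

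Three stronger readings are tempting but not supported:
- A reader might infer that the adjusted odds ratios are bound to be inflated or fail to converge. Most fits succeed: separation was 0% with seven terms and 10% at worst in the table.
- A reader might carry the inflation over to injurious falls. That outcome is reported as a rate, which points to rate ratios; the article never mentions odds ratios, and average bias there was small.
- A reader might conclude that the six adjusters should be cut, or prior falls dropped. Firth fits that kept all six had little bias, so cutting gives up confounder control for no demonstrated need. The models are described as predictive, and unadjusted results are planned as well, so prior falls is a legitimate term.

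**Conclusion.** The point holds for the risk-of-falling model. The six adjusters plus one candidate factor leave about 2 to 5 events per parameter on the article's own figures. Under an ordinary logistic fit the adjusted log odds ratios would be imprecise (power about 22% to 30% for an odds ratio of 2) and too large on average. The size was about 14% to 33% in most simulated settings and 9% in the mildest, with occasional separation when adjusters are categorical. The injurious-falls model, at about 15 to 28 events, is sparse too, but its risk is wide intervals and category terms that cannot be estimated.

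This rests on 78 evaluable participants, the article's faller and injury figures, a logistic model for the binary outcome (the article names none), and assumed covariate distributions. The event counts do not depend on the simulations; the bias percentages do. It affects a secondary aim, and not the primary estimate of the falls rate.

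**What to change.** Amend the modelling text before analysis:
- Keep all six prespecified adjusters.
- Fit the risk-of-falling model by Firth-type penalised likelihood, with penalised-likelihood confidence intervals.
- In the risk-of-falling and injurious-falls models, enter severity of ID, daily-living assistance and mobility as single scored terms.
- Report the risk-factor results for these two outcomes as exploratory.

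The all-falls count model can stay as planned. The Firth fit examined here treats participants as independent, so if the mixed model is meant to carry a random effect (for example for housemates), settle that at the same time. The cost is slight shrinkage of the estimates, an assumed linear trend across the levels of the scored adjusters, and a few lines of code. Recruitment and data collection do not change. The fix removes most of the bias and the separation; it does not supply the missing events, so intervals will stay wide.
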